### 2.9. Study Approvals

The conduct of this study was approved by the Northern Sydney Local Health District HREC (REGIS ID: 2025/ETH00118). The protocol for this study has been prospectively registered with the Australian New Zealand Clinical Trails Registry (ACTRN12625001354471, https://anzctr.org.au/ACTRN12625001354471.aspx, accessed on 19 December 2025).

## 3. Discussion

Severe stress and burnout in ED settings is prevalent and a growing concern, with significant implications for patient and staff wellbeing, the healthcare system, and public health. However, there remains a lack of evidence-based preventative proactive stress management strategies that are effective and accessible within healthcare settings. The WeCare proof-of-concept study aims to evaluate the feasibility, acceptability, and preliminary effectiveness of a wearable-integrated, self-guided program designed to improve mental and physiological wellbeing and stress regulation in high-stress clinical environments, such as ED settings. The program combines digital education, evidence-based stress reduction techniques, and real-time biofeedback via wearable sensor technologies to support self-regulation in day-to-day routine.

WeCare represents a forward-thinking self-managed model for early mental and physical health intervention that can be easily embedded in healthcare and, to our knowledge, has not previously been attempted. It leverages low-cost technology to address long-standing barriers such as mental health clinician shortages, long waitlists, stigma, and limited access to preventive care. By integrating evidence-based tools into a user-friendly, self-managed platform, it offers a scalable and promising solution for tackling distress and building resilience among vulnerable groups in high-stress healthcare environments.

The study will be conducted in a metropolitan hospital in Sydney, focusing on presenting patients with acute conditions (i.e., acute injury or medical complain) and frontline staff who are regularly exposed to high stress in this environment. Quantitative feasibility outcomes, including recruitment, retention, adherence, and data completeness, will help determine the program’s practical implementation in a real-world healthcare setting. Exploratory outcomes will assess changes in psychophysiological sources of distress, emotional exhaustion, sleep, mood, and perceived health, as well as healthcare use and work functioning. A qualitative component will capture participants’ experiences with the program, identifying enablers and barriers to engagement, which will guide future refinement and delivery. Importantly, any adverse events will be closely monitored and reported, contributing to a growing but still limited body of research on the safety of digital and wearable-based/digital interventions in healthcare settings.

Although this is a small-scale pilot, the insights gained from the study will lay the foundation for future trials involving larger and more diverse samples. If proven feasible and acceptable, *WeCare* has the potential to offer an effective, scalable, and sustainable approach to improving stress resilience and mental wellbeing in high-risk healthcare environments, ultimately contributing to better care, reduced costs, and a more resilient health workforce.

### Strengths and Limitations

The study is highly innovative and demonstrates several notable strengths. It targets under-served, high-risk populations with limited access to preventative mental health support. The intervention is novel in that it combines safe and widely accepted consumer-grade wearable technology with evidence-based stress management and wellbeing strategies delivered through digital tools, providing a scalable and low-cost model. A staggered multiple-baseline design and sequential mixed methods strengthened internal validity and allow for a nuanced understanding of user engagement and outcomes. Importantly, the study adopts a collaborative approach, incorporating input and feedback from end-users to co-design solutions that are acceptable, accessible, affordable, and beneficial, ensuring that the tools are tailored to real-world needs and preferences for sustained use [51]. As this paper describes a protocol rather than a completed study, these strengths relate to the proposed methodological approach and the anticipated value of the planned research. This protocol lays the foundation for a future fully powered trial and supports progression to subsequent implementation research.

While innovative, this study has limitations. Selection bias may occur due to the requirement for English proficiency, smartphone access, and digital literacy, potentially limiting participation from more diverse or disadvantaged groups. As expected in pilot research, where the main focus is on test feasibility, refining the intervention, and informing future trial design, the small planned sample size reflects the study’s exploratory nature and limits both generalisability and the ability to detect statistically significant effects. Adherence may also be influenced by the self-guided nature of the program, as digital interventions are often associated with higher attrition rates. To mitigate this, we incorporated both human and digital support strategies, including automated reminders, weekly check-ins, and engagement tracking. Potential expectation-related bias will also be addressed and minimised through transparent communication of the study’s exploratory aims during recruitment and onboarding.

## 4. Conclusions

Emergency care settings are inherently high-stress environments that present unique challenges for both patients and healthcare staff. By combining physiological monitoring with self-guided interventions delivered through personalised feedback, *WeCare* offers an innovative, wearable-integrated solution with the potential to enhance resilience, prevent serious mental health issues, and improve long-term wellbeing of vulnerable groups in EDs. This pilot study will generate critical evidence for wearable-supported wellbeing interventions, informing future research, service design, and clinical practice in emergency care settings.

## Figures and Tables

**Figure 1 sensors-26-00104-f001:**
[figure not shown]
Flow map of the WeCare program pilot evaluation in emergency care settings.

**Figure 2 sensors-26-00104-f002:**
[figure not shown]
Experimental design and timeline of a single-case multiple-baseline experiment across participants with three tiers. Participants begin a 1–3-week baseline (usual care) phase, followed by a 6-week WeCare intervention. A staggered multiple-baseline design offsets intervention start: Tier I ~ Day 7 (1st week), Tier II ~ Day 11 (2nd week), Tier III ~ Day 15 (3rd week), providing within-person controls until the intervention begins.

**Figure 3 sensors-26-00104-f003:**
[figure not shown]
WeCare program: weekly themes, suggested activities, and reflection prompts.

**Table 1 sensors-26-00104-t001:** Detail of experimental phases.

Phase	When It Starts	How Long	Device Used	What Happens
Baseline (Usual care)	*Sample* 1 and 3: 0–2 weeks post-ED care. *Sample* 2: 4–6 weeks post-ED care. *Sample* 4: Any time.	1–3 weeks (7, 11, 15 days by tier)	“Blinded” smartwatch (wrist device)	- In-person onboarding. - Wear smartwatch daily. - Smart ring sized for next phase. - Continue usual care, no changes. - Daily diaries and weekly surveys.
WeCare Program (Intervention)	After baseline phase ends	6 weeks (staggered by tier)	“Blinded” smartwatch Smart ring	- In-person onboarding. - Continue smartwatch monitoring. - Start intervention using a digital health platform and a smart ring as companions to track real-time physiological data and receive personalised education/feedback.
Optional Extension (Device testing)	After intervention phase ends	2 weeks	“Blinded” smartwatch	- Smartwatch (instead of smart ring) as intervention companion. - Test delivery method only. - Part of qualitative, co-design acceptability analysis.

**Table 2 sensors-26-00104-t002:** Participants’ inclusion and exclusion criteria.

Participant Group	Inclusion Criteria	Exclusion Criteria
All	Aged 18–70 years. Sufficient English proficiency. Willing to wear a smart watch and a smart ring * device for at least 22 hours per day for the next 3 months. * Comfort or infection-control issues related to wearing hand/wrist devices will be monitored and addressed as needed.	History or evidence of substance abuse (e.g., alcohol or illicit drugs) at the time of admission. History of severe mental health disorders, e.g., bipolar disorder or psychoses or chronic depression disorder, determined by medical history or interview. History of unstable or poorly controlled cardiovascular, neurological, or other serious systemic disease that is likely to interfere with study evaluation or participant safety (e.g., uncontrolled blood pressure, unstable arrhythmia, decompensated heart failure, recent myocardial infarction or stroke, and new or uncontrolled metabolic or inflammatory conditions). Evidence of any conditions (e.g., cognitive disorder or dementia) that interfere with the patient’s ability to understand the requirements of the study and their ability to consent. Undergoing, or planning to undergo, surgery or inpatient admission/hospitalisation within the next three months.
Mild-to-moderate injury patient group (*Sample* 1)	Sustained in last 2 weeks a minor-to-moderate injury due to traumatic unintentional cause (e.g., traffic crash, fall, or work-related), such as a whiplash injury, minor fractures, limb fractures, or joint sprains or strains. Presented to RNSH emergency department (ED), Sydney, Australia. Injury Severity Score (ISS) < 15.	Injuries due to assaults or self-harm, because they are often associated with severe additional psychological stress or trauma. Injuries involving the brain. Very minor, localised, superficial soft-tissue injuries, such as small cuts, abrasions, minor bruises, or localised swelling.
Severe injury patient group (*Sample* 2)	Sustained in last 4 weeks a severe traumatic injury due to non-violent cause (e.g., traffic crash, fall, or work-related), such as multi-trauma or severe injuries requiring aggressive therapy and/or admission to the Intensive Care Unit (ICU). Presented to RNSH ED, Sydney, Australia. ISS ≥ 15.	Injuries due to assaults or self-harm. Injuries involving the brain. Very minor, localised, superficial soft-tissue injuries, such as small cuts, abrasions, minor bruises, or localised swelling.
Medical patient group (*Sample* 3)	Acute onset of medical symptoms of minor-to-moderate severity, such as gastrointestinal symptoms (e.g., abdominal pain or nausea), urinary symptoms (e.g., urinary tract infections), respiratory symptoms (e.g., mild shortness of breath or persistent cough), migraine, or non-traumatic musculoskeletal symptoms (e.g., chronic or spontaneous back pain, neck pain), prompting an ED visit in last 2 weeks. Presented to RNSH ED, Sydney, Australia. Received a green triage code (Australasian Triage Scale (ATS) category 3–5 = less urgent). Requiring standard treatment home or inpatient non-ICU.	Received a yellow, red, or blue triage code, requiring aggressive or palliative treatment, intubation, or ICU admission. Trauma-related musculoskeletal conditions (e.g., fracture, whiplash, or sprain from a fall/crash).
ED healthcare staff (*Sample* 4)	Being a healthcare worker at the ED of RNSH, Sydney, Australia, including medical doctors, nurses, paramedics, and allied health professionals.	History of injury requiring ED presentation or exposure to a traumatic event (i.e., perceived threat of injury to self or others) in the past year. Presented to the ED or admitted to hospital in the past year.

ATS: Australasian Triage Scale; ED: Emergency Department; ICU: Intensive Care Unit; ISS: Injury Severity Score; RNSH: Royal North Shore Hospital.

**Table 3 sensors-26-00104-t003:** Description of study outcomes for the experimental component.

**(a) PRE-BASELINE MEASURES**	OUTCOME	Data Collection	Day 0	Daily	Ecological *	Weekly	Pre-Program	Post-Program	Follow-Ups
Socio-demographic	Seven multiple-choice questions	Online/Paper	✓	-	-	-	-	-	-
Clinical	Medical and mental health history	Online/Paper	✓	-	-	-	-	-	-
	Treatment and medication use	Online/Paper	✓	-	-	-	-	-	-
	Lifestyle habits	Online/Paper	✓	-	-	-	-	-	-
Psychosocial	PSI stress	Online/Paper	✓	-	-	-	-	-	-
	PSI wellbeing	Online/Paper	✓	-	-	-	-	-	-
	PSI psychological distress	Online/Paper	✓	-	-	-	-	-	-
	PSI abnormal illness behaviour	Online/Paper	✓	-	-	-	-	-	-
	PSI quality of life	Online/Paper	✓	-	-	-	-	-	-
	Pain Catastrophising Scale	Online/Paper	✓	-	-	-	-	-	-
	Injustice Experience Questionnaire	Online/Paper	✓	-	-	-	-	-	-
	Composite Scale of Morningness	Online/Paper	✓	-	-	-	-	-	-
	Brief Resilience Scale	Online/Paper	✓	-	-	-	-	-	-
	General Self-Efficacy Scale	Online/Paper	✓	-	-	-	-	-	-
**(b) PRIMARY OUTCOMES**	OUTCOME	Data collection	Day 0	Daily	Ecological *	Weekly	Pre-program	Post-program	Follow-ups
Mental health status	Subjective Units of Distress Scale	Online/Paper	✓	✓	✓	-	-	✓	✓
Sleep quality	Numeric Rating Scale (0 to 10)	Online/Paper	✓	✓	-	-	-	✓	✓
Autonomic function	HRV metrics	Wearable devices	-	✓ **	-	-	-	✓ **	✓ **
Sleep function	Sleep metrics	Wearable devices	-	✓ **	-	-	-	✓ **^	✓ **^
**(c) GENERALISATION MEASURES**	OUTCOME	Data collection	Day 0	Daily	Ecological *	Weekly	Pre-program	Post-program	Follow-ups
‘Proximal’ Generalisation Measures									
Mental health function	Perceived Stress Scale	Online/Paper	✓	-	-	✓	-	✓	✓
	Patient Health Questionnaire	Online/Paper	✓	-	-	✓	-	✓	✓
	PTSD Checklist for DSM-5	Online/Paper	✓	-	-	✓	-	✓	✓
	Generalised Anxiety Disorder Questionnaire	Online/Paper	✓	-	-	✓	-	✓	✓
Sleep	The Pittsburgh Sleep Quality Index	Online/Paper	✓	-	-	✓	-	✓	✓
Adverse events and life stressors	Self-reported adverse events and stressors diaries	Online/Paper	✓	-	-	✓	-	✓	✓
Consumer perception	Numeric Rating Scale (−7 to +7)	Online/Paper	✓	-	-	✓	-	✓	✓
Quality of life	EQ-5D-5L—Health score (0 to 100)	Online/Paper	✓	-	-	✓	-	✓	✓
Physiological status	HR, RR, Sp02, activity, summary scores, temp	Wearable devices	-	✓ **	-	-	-	✓ **^	✓ **^
‘Distal’ Generalisation Measures									
Mental wellbeing	The World Health Organisation-Five Well-Being Index	Online/Paper	-	-	-	-	✓	✓	✓
Cognitive functioning	Perceived Deficits Questionnaire	Online/Paper	-	-	-	-	✓	✓	✓
Pain interference	Numeric Rating Scales (0 to 10)	Online/Paper	-	-	-	-	✓	✓	✓
Fatigue	Numeric Rating Scales (0 to 10)	Online/Paper	-	-	-	-	✓	✓	✓
Social participation	WHODAS 2.0 Participation Domain	Online/Paper	-	-	-	-	✓	✓	✓
Consumer satisfaction	Was-It-Worth-It Questionnaire	Online/Paper	-	-	-	-	✓	✓	✓
Continuation of use	Three custom questions	Online/Paper	-	-	-	-	-	✓	✓

* Every 2 h for a maximum of 4 days (2 during baseline phase, 2 during intervention phase); ** Continuous monitoring using wearables; ^ If participants are willing to continue the wearable-based self-monitoring past the 11 weeks. ✓ Measured at the specific time point.

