**Experimental phases:**

Table 1 and Figure 2 provide a schematic overview of the experimental study design, phases, and timeline. Each single-case experiment, including at least three tiers, begins with a **(i) Baseline phase (usual care)** of 1–3 weeks, with duration randomised for each participant, followed by a **(ii) Intervention phase (WeCare program)** of 6 weeks. A staggered, multiple-baseline design is used: all participants start the baseline at the same time, but the intervention begins at different times (Tiers I–III)—approximately 7 days (end of the 1st week) for Tier I, 11 days (midpoint of the 2nd week) for Tier II, and 15 days (start of the 3 week) for Tier III. This ensures robust within-person controls and reducing external bias. The minimum 7-day baseline allows for the collection of at least five observations, ensuring maximum rigour [59], while accommodating day-to-day variability (e.g., “bad day”) and logistical constraints (e.g., participant availability for an in-person visit). During the Baseline phase, participants will be provided with a *smartwatch* device (Vivoactive 5, Garmin Ltd., Schaffhausen, Switzerland, https://www.garmin.com/en-AU/legal/compliance/, https://www.garmin.com/en-AU/p/1057989/; accessed on 15 October 2025), worn on the wrist for continuous physiological monitoring through the whole study. The device’s display will remain blank, and participants will not have access to any feedback or vital sign data. They will be instructed to continue their daily routines and usual care practices without changes to medication, lifestyle, or activities. To support retention and maintain engagement during the baseline phase, participants will receive one to two brief messages per week acknowledging their data collection and encouraging continued participation. Regular contact of this kind has been shown to improve adherence and reduce attrition in single-case and digital health intervention studies [60].

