At the start of the Intervention phase, participants will receive a *smart ring* device (OuraRing4, Oura Health, Oulu, Finland, https://ouraring.com/terms-of-use, https://ouraring.com; accessed on 15 October 2025), which will serve as their companion device for the *WeCare* program. Unlike the smartwatch, the smart ring allows participants to view their physiological data in real time through an associated app and provides personalised guidance to support behavioural and lifestyle modifications. Each of the above phases will begin with an in-person session that includes participant education, device setup, and usage instructions. Alternatively, this session may be delivered via telehealth or through a pre-recorded video, with the device mailed or couriered to participants. Following the intervention, an optional **(iii) Extension phase** of 2 weeks will be offered, allowing participants to experience the program using the smartwatch as an alternative wearable. This phase will be an integral part of the “acceptability” evaluation conducted during the co-design component and is not intended to test effectiveness. Follow-up assessments will be conducted at 3 and 6 months post-intervention.

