Once a cohort of at least 3 eligible participants is recruited, they will be enrolled concurrently, assigned a unique study number, and booked in for the introductory session. Participants will be randomly allocated to a baseline phase duration of 1, 2, or 3 weeks (i.e., 7, 11, or 15 days, respectively) depending on their tier, in accordance with the study’s single-case design standards. An independent researcher, not involved in participant recruitment, will generate a randomisation sequence using standard computerised methods to minimise bias. Randomisation will take place after the pre-baseline data is collected (Week 0) to reduce the risk of allocation bias. Investigator blinding is not feasible due to study procedures, and this is not a randomised clinical trial.

All participants who choose to enrol in the study will be automatically included in all three components of this proof-of-concept study. Upon completion of the *WeCare* program as the experimental component, research investigators will invite participants to take part in in-depth interviews. Additionally, cost data will be collected weekly throughout the duration of the study.

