### 2.5. Intervention: WeCare Program

WeCare is an innovative, evidence-based, wearable-integrated wellbeing initiative designed for individuals exposed to significant stress. It delivers a 6-week, self-directed and self-reflective intervention program aimed at improving stress regulation, enhancing resilience, promoting sustainable recovery, and optimising performance and wellbeing. The program integrates biometric wearable monitoring with psychoeducation and personalised behavioural guidance to mitigate the risk of disability associated with acute (e.g., injury, trauma, or illness), chronic, or occupational stress (e.g., ED workers).

Co-designed by a multidisciplinary team of experts in mental health, injury recovery, and rehabilitation, together with individuals with lived experience, WeCare empowers participants to take charge of their health by combining real-time physiological data from wearables and behavioural science through personalised, data-informed feedback, and expert guidance.

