#### 2.5.3. Program Structure

Participants will be guided through the following steps (Figure 3):(1)*Making sense of stress and wellbeing* (Week 1)

Participants attend a 60–90 min psychoeducation session, delivered in person at the RNSH laboratory, or via telehealth as a pre-recorded video. This session introduces the multidimensional nature of stress and wellbeing, including its physiological manifestations. Participants are introduced to the smart ring, instructed on installation of the app, and begin continuous data and daily activity tracking. The goal of this session is to build foundational awareness and context-specific understanding of stress and wellbeing.

(2)*Knowledge is power: digging into the data* (Weeks 2–3)

Participants explore their personal biometric data to improve body awareness and recognise stress and recovery patterns. This phase encourages reflection through guided prompts and educational content, helping participants identify how stress manifests in their physiology and daily routine. The aim is to foster insight and engagement with one’s own health data as a tool for learning and growth, supporting meaningful changes. A 2-week period is required by the smart ring system to calibrate personalised recommendations for each participant.

(3)*In the driver’s seat: taking charge of my health* (Weeks 4–6, and beyond)

This final phase encourages behavioural change through experiential learning. Participants learn about healthy habits and are encouraged to self-reflect and experiment with a range of self-regulation strategies to manage stress and enhance wellbeing, such as the app’s in-built breathwork and mindfulness modules, and integrate these practices into their daily routines. Following Week 6, participants will have the option to continue the intervention for an additional two weeks using a smartwatch instead of the smart ring. Guidance will also be provided on how to design and run a personalised self-experiment beyond the core 6-week program, encouraging sustained engagement and long-term habit formation.

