**(b)** 
**Primary outcome measures**

Primary outcomes are the target behaviours directly addressed by the intervention. These are assessed daily, throughout the baseline and intervention phases (including at enrolment, Week 0), post-intervention (within 2 weeks of the final session), and at 3- and 6-month follow-ups. They include the following clinical self-report (daily diary) and psychophysiological outcomes of stress regulation, selected for their sensitivity to change and appropriateness for single-case designs.

**
*Clinical self-report outcomes:*
**
*Psychological distress*: Daily ratings of 24 h average distress measured with the 1-item Subjective Units of Distress Scale (SUDS), ranging from 0 (no distress) to 100 (extreme distress) [69], plus ecological momentary assessments every 2 h for 4 days only (2 during baseline and 2 during intervention).*Sleep quality*: Measured each morning using a single-item scale from 0 (worst) to 10 (best), aligned with self-reported wake times to minimise recall bias.
***Psychophysiological outcomes*:** Continuously recorded via a smartwatch using photoplethysmography and an accelerometer. Adherence and data completeness will be monitored via app analytics and automated tracking tools.
*Heart rate variability (HRV) metrics*: Reflects autonomic nervous system (ANS) activity. Higher parasympathetic (vagal) tone indicates improved regulation, whereas low HRV is associated with mental health risk [37,38,39]. HRV Root Mean Square of Successive Differences (HRV-rMSSD) and other time-, frequency-, and nonlinear-domain and composite metrics will be extracted from beat-to-beat intervals, especially during overnight monitoring.*Sleep parameters*: Includes sleep duration, bedtime, sleep onset latency, nocturnal heart rate, wake-up time, and sleep-related temperature deviation (if available).

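### Follow-up wearable sleep, a primary outcome, is taken only from participants who choose to keep self-monitoring; HRV from the same watch carries no such condition, and agreed wear ends before either follow-up

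*Protocol article*

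**What the plan says.** - **Section 2.6.2(b), primary outcome measures.** The primary outcomes are the SUDS distress rating, a 0–10 sleep-quality rating, HRV metrics and sleep parameters. The last two are recorded by smartwatch. All four are to be assessed daily through baseline and intervention, then "post-intervention (within 2 weeks of the final session), and at 3- and 6-month follow-ups". No condition is attached.
- **Section 2.2.1, experimental phases.** Follow-up is dated from the end of the program: "Follow-up assessments will be conducted at 3 and 6 months post-intervention". The smartwatch is "worn on the wrist for continuous physiological monitoring through the whole study", with a blank display and no feedback to the wearer.
- **Table 2, criteria for all groups.** Participants must be willing to wear the watch and ring "for at least 22 hours per day for the next 3 months".
- **Table 1.** No device phase is listed after the optional 2-week extension.
- **Table 3.** The sleep-metrics row and the physiological-status row carry the mark ^ at post-program and at follow-ups. The mark means: "If participants are willing to continue the wearable-based self-monitoring past the 11 weeks". The HRV row is marked for continuous wearable monitoring but has no ^. SUDS, the 0–10 sleep rating, the weekly questionnaires and the distal measures are collected online or on paper at follow-up, also without ^.

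**The concern.** Two primary outcomes come from one watch worn on the same nights. The text schedules both at follow-up without condition. The table makes one of them depend on the participant's later choice and leaves the other unconditional, and the agreed period of wear covers neither follow-up. Site staff cannot tell from the article whether a participant who has stopped using wearables should be asked to put the watch back on.

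The choice is made after the program and may well be related to how engaged the participant was or how much they felt they gained. The footnote also refers to continuing *self-monitoring*, not just to wearing the blank study watch. Tracking one's own data is one of the three program elements in section 2.5.2. Read literally, the ^ rows at follow-up describe people still using part of the program, set against a baseline recorded without feedback. That is a different quantity from the state of all participants 3 or 6 months after a 6-week program. Experiments may have as few as three participants, so each non-continuer removes a third of an experiment's follow-up wearable sleep data.

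**Working it through.** **Inputs.** Baseline is 7, 11 or 15 days by tier (section 2.4, Table 1). The program lasts 6 weeks = 42 days (section 2.5). The optional extension is 2 weeks = 14 days (section 2.5.3). Follow-ups are at 3 and 6 months post-intervention (section 2.2.1). Wear is agreed for 3 months (Table 2). Assumptions: 3 months ≈ 91 days, 6 months ≈ 182 days, and the wear period runs from the start of baseline.

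**The plan's own figure, 11 weeks.** With the nominal 3-week baseline, 3 + 6 + 2 = 11 weeks, so the footnote's figure reproduces. With the actual day counts the same period is 7 + 42 + 14 = 63 days (9.0 weeks) to 15 + 42 + 14 = 71 days (10.1 weeks). Agreed wear of 91 days therefore covers baseline, program and extension.

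**Gap to the follow-ups.** Program end = baseline + 42. Follow-up day = program end + 91 or + 182. Gap = follow-up day − 91.

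| Baseline (days) | Program end (day) | 3-month follow-up (day) | Gap | 6-month follow-up (day) | Gap |
|---|---|---|---|---|---|
| 7 | 49 | 140 | 49 d = 7.0 wk | 231 | 140 d = 20.0 wk |
| 11 | 53 | 144 | 53 d = 7.6 wk | 235 | 144 d = 20.6 wk |
| 15 | 57 | 148 | 57 d = 8.1 wk | 239 | 148 d = 21.1 wk |

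These are two separate clusters, not one continuous range.

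**Sensitivity.**
- A nominal 21-day baseline gives gaps of 9 and 22 weeks.
- Taking 3 months as 12 weeks gives 7.0–8.1 and 19.0–20.1 weeks. The 3-month gap does not move, because the wear period and the follow-up interval are both 3 months and cancel.
- Counted from the footnote's 11 weeks (77 days), the follow-ups fall 9.0–10.1 and 22.0–23.1 weeks later.
- Any wait between enrolment and baseline would widen the gaps if the 3 months run from enrolment.

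**Post-program cells.** That visit is within 2 weeks of the final session, so it falls no later than week 9.0–10.1, or week 11 with a nominal 3-week baseline. It is not past 11 weeks, so the ^ in those cells has nothing to act on.

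**Loss per experiment of three.** One non-continuer removes 1/3 of the follow-up wearable sleep data, and two remove 2/3.

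**The case against.** Much of the follow-up is untouched. SUDS and the 0–10 sleep rating are primary outcomes taken without condition, as are PSS, PHQ-9, PCL-5, GAD-7, PSQI, the EQ-5D health score and the distal measures. A reader might infer that durability is measured only in continuing users. Table 3 does not support that: the restriction concerns wearable data.

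HRV is not conditional in Table 3, so its restriction is inferred from the lapsed wear period. Nor does wearing the blank watch amount to continued tracking, because section 2.5.2 defines that element through the wearable app. The self-monitoring argument applies only to the ^ rows.

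The Table 2 criterion is a screening question and does not forbid later wear. The phrase about the whole study may mean the experimental phases only. It would therefore go too far to say that the wear criterion, that phrase, Table 3 and section 2.6.2(b) are all mutually incompatible. The firm conflicts are narrower: ^ against section 2.6.2(b), and ^ on sleep but not on HRV.

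Device logistics at follow-up may well be left to the full protocol. The article is also open about being an exploratory pilot with limited ability to detect effects.

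All of this stands and limits the point. It does not remove it, because the article states the rule for a primary outcome in two different ways, which is more than leaving out detail.

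**Conclusion.** The point holds for wearable outcomes at follow-up. As written, wearable sleep (a primary outcome) and physiological status are observed at 3 and 6 months only in participants who choose to continue. HRV probably will be too, because agreed wear ends about 7–8 weeks before the first follow-up and 20–21 weeks before the second. This rests on counting 3 months as about 13 weeks from the start of baseline.

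A reader might go on to infer that the bias favours the program by some stated factor. The documents give no continuation rate and no link between continuing and benefit. People with persisting distress might equally be the ones who keep monitoring. The direction and size are unknown.

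The baseline-versus-intervention comparison and the self-report follow-up do not depend on this. It is a correction worth making before follow-up data are collected, and it does not undermine the main comparison.

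**What to change.** Reconcile section 2.6.2(b), the wear criterion in Table 2, and the HRV, sleep and physiological-status rows of Table 3, in one of two ways.

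1. **Keep the wearable follow-up.** At consent, ask every participant to wear the blinded smartwatch for a short fixed window at each follow-up, whether or not they still self-monitor. Seven days would match the shortest baseline. Remove ^ from the follow-up cells and add the two windows to the wear criterion. The cost is some participant burden and device logistics: courier, set-up and data checks. Section 2.2.1 already allows devices to be mailed or couriered, but the article does not say whether watches are returned or available for re-issue, so the cost cannot be stated from it.
2. **Demote it.** Remove HRV and wearable sleep from the follow-up primary outcomes and label them optional and descriptive. Report how many participants contribute, split by the continuation-of-use answers that Table 3 already collects, and draw no durability conclusion from them. The cost is a text change and the loss of any physiological statement about persistence.

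In either case, remove ^ from the post-program cells of the sleep and physiological-status rows.
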